#### Randomization and blinding

3.2.5

A biostatistician, not involved in the trial, will randomize all eligible participants using a computer-generated random number list. Group assignments will be concealed in consecutively numbered sealed envelopes that will be opened sequentially upon the enrollment of each participant. Eligible subjects will be randomly allocated into two groups: the multicomponent exercise group and the control group. Participants and interveners will not be blinded to the intervention assignment due to the nature of exercise intervention. However, outcome assessors and data analysts will be blinded to group assignments.

#### Measurement

3.2.6

##### RCT

3.2.6.1

The measurements in this trial will consist of basic characteristics, physical frailty, cognitive performance, body composition, senior fitness, self-efficacy for exercise, anxiety, depressive symptoms, sleep quality, and health-related quality of life. Exercise self-efficacy will be chosen as the mediating factor. Physical frailty and cognitive function will be considered as the primary outcomes, while the rest are secondary outcomes. All these variables will be assessed at baseline and at the end of the intervention period. Additionally, we will collect data on adherence, dropout rate, satisfaction, and adverse events as complementary measures. Trained research assistants specializing in geriatrics will conduct these assessments.

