#### Sample size estimation

3.2.4

For the RCT, the sample size will be calculated using PASS software, based on improvement in the primary outcome (physical frailty) in this trial. Previous findings from a similar exercise program reported a reduction in physical frailty score of 0.22 in the control group and 1.59 in the intervention group (Sadjapong et al., 2020). Given a power of 90% and level *α* = 0.05, 34 participants are needed. Considering a 20% attrition rate, with 41 participants in each group, a total of 82 participants are needed. Regarding the qualitative interviews, a purposive subsample of 20 participants who have completed the multicomponent exercise intervention will be recruited.

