#### Data analysis

3.2.10

Summary statistics, including means with standard deviations, frequencies, and percentages, will be generated for baseline characteristics. To compare the baseline characteristics between the two groups, Student’s *t*-test or the Wilcoxon rank-sum test will be utilized for continuous variables, while Chi-square or Fisher’s exact tests will be employed for categorical variables. Analysis of covariance (ANCOVA) and generalized linear models (GLM) will be performed to compare mean changes in continuous variables between the two groups. Adherence, dropout rates, program satisfaction, and adverse events will be tabulated and summarized using descriptive statistics. Mediation models will be used to test whether exercise self-efficacy mediates the relationship between the multicomponent exercise intervention and physical frailty, cognitive function, body composition, senior fitness, mental health, sleep quality, and health-related quality of life. Any missing data on outcomes will be approximated through multiple imputation. All analyses will be performed with the intention-to treat (ITT) principle. Two-sided tests will be performed for all analyses, and *p*-value less than 0.05 will be considered to be statistical significance. Additionally, sensitivity analyses will be adopted to assess the robustness of the findings based on the per-protocol analysis set.

Regarding qualitative data, audio-recorded interview will be transcribed word-for-word. Content analysis will be adopted to code the data on their perceptions of the intervention. Two authors will independently code the data, and any discrepancies will be resolved through discussion.

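### Two primary outcomes are each tested at 0.05 with no stated success rule, order or multiplicity control, while the sample size treats physical frailty as the only primary outcome

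*Protocol article*

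**What the plan says.** Section 3.2.6.1 (RCT) states that "Physical frailty and cognitive function will be considered as the primary outcomes, while the rest are secondary outcomes". The abstract names the same two outcomes as primary. Cognitive function is measured by the MoCA.

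Section 3.2.10 (Data analysis) states that "Two-sided tests will be performed for all analyses" and that a p-"value less than 0.05 will be considered to be statistical significance". It plans ANCOVA and generalized linear models for mean changes in continuous variables. It gives no testing order, no split of alpha, no multiplicity adjustment and no rule on whether one or both primary outcomes must be significant.

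Section 3.2.4 (Sample size estimation) bases the calculation on "based on improvement in the primary outcome (physical frailty) in this trial", in the singular. The effect comes from an earlier study that "reported a reduction in physical frailty score of 0.22 in the control group and 1.59 in the intervention group". The section begins its result with "Given a power of 90% and level" alpha = 0.05, finds that "34 participants are needed", and continues: "Considering a 20% attrition rate, with 41 participants in each group, a total of 82 participants are needed". It gives no effect, standard deviation or power for the MoCA.

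**The concern.** With two primary outcomes and one flat threshold, the text lets a significant result on either be reported as a primary success at the full 0.05. The error rate for a primary claim by the trial is then not the nominal 5%.

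The sections also disagree on how many primary outcomes there are: two in the abstract and section 3.2.6.1, one in section 3.2.4. A reader cannot tell which result would make the trial positive, or what the 90% power refers to at trial level. A rule chosen after the results are known would not be credible.

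**Working it through.** **Inputs from the article.** Two primary outcomes (3.2.6.1); two-sided 0.05 for every analysis (3.2.10); 90% power, frailty reductions of 0.22 and 1.59, n = 34, 20% attrition and 41 per group (3.2.4).

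**Inputs that are assumptions.** The correlation between the two test statistics, the MoCA effect size, and the correlation r between baseline and follow-up MoCA. The article gives none of these.

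**1. The plan's own figure.** The difference is 1.59 − 0.22 = 1.37 points. No standard deviation is given, so n = 34 cannot be reproduced directly. Reading 34 as per group and solving backwards with the normal approximation:

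d = √(2/34) × (1.960 + 1.282) = 0.786, so the implied SD is 1.37 / 0.786 ≈ 1.74.

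The 90% power is thus power for frailty at a standardized effect of about 0.79. Nothing in the calculation concerns the MoCA.

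**2. If success on either outcome counts.** For independent tests the chance of at least one false positive is 1 − 0.95² = 0.0975. For correlated tests it is 1 − P(|Z₁| < 1.96 and |Z₂| < 1.96) under a bivariate normal:

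| Correlation | At least one false primary claim |
|---|---|
| 0 | 9.75% |
| 0.3 | 9.5% |
| 0.5 | 9.1% |
| 0.7 | 8.3% |
| 0.9 | 7.0% |

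**3. If both must succeed.** There is no inflation, because a false claim needs at least one true null hypothesis to be rejected at 0.05. The chance of success is then no higher than the smaller of the two powers, so it depends on the MoCA, for which no power is given.

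**4. What the trial can detect on the MoCA.** Analysable participants: 41 × 0.8 = 32.8, about 33 per arm. An unadjusted two-sided t-test reaches 90% power at d ≈ 0.81. ANCOVA on baseline reduces the residual SD by √(1 − r²), so the detectable d shrinks by the same factor:

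- r = 0: 0.81
- r = 0.5: 0.81 × √0.75 ≈ 0.70
- r = 0.7: 0.81 × √0.51 ≈ 0.58

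Power at assumed MoCA effects, 33 per arm:

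| Assumed d | r = 0 | r = 0.5 | r = 0.7 |
|---|---|---|---|
| 0.3 | 22% | 28% | 39% |
| 0.5 | 52% | 64% | 80% |
| 0.6 | 67% | 79% | 92% |

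**5. Cost of splitting alpha.** At 0.025 per outcome and d = 0.786 with 34 per arm, frailty power falls from 90% to about 84% by the normal approximation: Φ(0.786 × √17 − 2.241) = Φ(1.00) ≈ 0.84. A fixed sequence that starts with frailty avoids this loss.

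**The case against.** The strongest reply is that the article never says either outcome suffices. Section 3.1 lists the outcomes together in one hypothesis, cognitive frailty is defined by both deficits, and the discussion speaks of improving both kinds of function at once. A both-must-succeed reading is possible, and under it type I error is not inflated. This stands: the inflation is conditional. But the article does not state that rule either, and under it the 90% does not describe the chance of success.

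A second reply is that a condensed article may leave multiplicity to the full protocol or analysis plan, and that a 0.05 threshold is compatible with a fixed sequence. The second half is true: the sequence proposed below also uses 0.05 twice. But the article is not silent. It fixes one threshold for all analyses and counts its primary outcomes differently in different sections, so the visible text needs reconciling.

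Three stronger readings are tempting, and the document does not support them:

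- A reader might infer that the false-positive rate is nearly doubled as a matter of fact. That needs the either-outcome rule and low to moderate correlation.
- A reader might infer that the article claims 90% power for cognition. Section 3.2.4 ties its calculation openly to physical frailty.
- A reader might infer that a null MoCA result would be uninterpretable, or that the MoCA test needs d of about 0.81. The ANCOVA estimate and its confidence interval would still inform, though perhaps imprecisely, and 0.81 is only the figure with no gain from baseline adjustment. The restricted MoCA entry range of 18 to 25 may lower r, so the true value is unknown.

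**Conclusion.** The point holds in a conditional form. What the text establishes is two primary outcomes, a flat two-sided 0.05, no decision rule, and sizing on one outcome described as the primary outcome.

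The consequence depends on the missing rule. Under an either-outcome rule, the error for a primary claim exceeds 5% at every correlation examined. Under a both-outcomes rule, the error is controlled but the chance of success is unstated and cannot exceed the MoCA power. As written, the text permits the first use.

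The error rates rest on the threshold in the article and an assumed correlation. The MoCA figures rest on assumed effects, an assumed r and 33 analysable per arm, and should be read as a range.

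**What to change.** Before unblinding, state the decision rule in section 3.2.10 and make sections 3.2.4 and 3.2.6.1 agree with it:

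- Test the Fried score first at two-sided 0.05. Test the MoCA at two-sided 0.05 only if the first test is significant.
- Say in section 3.2.4 that the 90% power applies to physical frailty only.
- Give the detectable MoCA difference for the planned ANCOVA as a range, with the assumed baseline correlations shown.

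This takes a few sentences and needs no additional participants. It holds the error across the two primary outcomes at 5% and leaves frailty power unchanged. The price is that a MoCA effect could not be claimed as confirmatory if frailty is not significant.

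If a standalone MoCA claim is wanted, Holm's procedure is the alternative. It costs some frailty power: with 34 per arm, power can fall towards about 84%, the value under a full split at 0.025, when the MoCA test does not succeed. If the intention is that both outcomes must succeed, say so and report the joint power instead.

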###### Basic characteristics

3.2.6.1.1

Participants’ demographic characteristics (e.g., age, sex, education, marital status, living arrangements, occupation, and income), lifestyle information (drinking and smoking), comorbidities, and medication use will be collected using a self-designed questionnaire.

###### Mediating factor

3.2.6.1.2

The Self-Efficacy for Exercise (SEE) Scale is a self-report of exercise self-efficacy. This scale has a range of total scores from 0–90. A higher score indicates higher self-efficacy for exercise (Resnick and Jenkins, 2000).

###### Primary outcomes

3.2.6.1.3

Physical frailty will be measured according to the Cardiovascular Health Study criteria (Fried et al., 2001) to enable comparability. The assessment includes five components:

Shrinking: Determined by unintentional weight loss exceeding 4.5 kg or more than 5% of body mass in the past 12 months.Weakness: Assessed through Body mass index (BMI) and sex-adjusted handgrip strength. Men cut-off points: 29, 30, and 32-kg handgrip strength for normal-weight, overweight and obese, respectively. Women: 17, 17.3,18, and 21 kg for underweight, normal-weight, overweight and obese, respectively.Exhaustion: Assessed by the frequency of fatigue in the last week using two items of the Center of Epidemiological Studies-Depression Scale (CES-D) (Orme et al., 1986).Slowness: Determined by height- and sex-adjusted gait speed. Cut-off points are 0.65 m/s of walking speed over a 4.57-m distance for men and women ≤173 cm and ≤ 159 cm, respectively, and 0.76 m/s for height above these ranges.Low physical activity: Assessed using the International Physical Activity Questionnaire-Short Form (IPAQ-SF). Energy expenditure (kcal/week) will be calculated for each participant, and low physical activity will be identified by an expenditure of <383 kcal/week in men and < 270 kcal/week in women (Brunner et al., 2018; Piotrowicz et al., 2023).

Individuals will be categorized into three groups based on their total score: robust (0), prefrail (1–2), and frail (3–5) groups (Fried et al., 2001). For this study, frailty status will be classified into two groups: the frail group (1–5) and the robust group (0).

The Montreal Cognitive Assessment (MoCA) is a brief screening tool for global cognition that reveals mild cognitive impairment and an early stage of Alzheimer’s disease (Nasreddine et al., 2005). This tool evaluates various cognitive domains, including attention, concentration, executive function/visuospatial ability, memory, language, conceptual thinking, calculations, and orientation. MoCA scores range from 0 to 30, with scores of 26 and higher generally considered normal. Scores falling between 25 and 18 indicate mild cognitive impairment, while scores lower than 18 are indicative of Alzheimer’s disease (Nasreddine et al., 2005). The Chinese version of MoCA (Beijing version) is widely utilized in China due to its established validity, reliability, and sensitivity (Yu et al., 2012).

###### Secondary outcomes

3.2.6.1.4

Body composition assessment will be conducted using the InBody S10. BMI will be calculated by dividing weight in kilograms by the square of height in meters. The senior fitness test battery referred to *Senior Fitness Test Manual, Second Edition* (Rikli and Jones, 2013), will be performed in the following order to minimize fatigue: (1) chair stand test (lower-body muscular strength); (2) arm curl test (upper-body muscular strength); (3) chair sit-and-reach test (flexibility); (4) back scratch test (flexibility); (5) 2.4-meter up-and-go test (dynamic balance); (6) single leg stand test (dynamic balance); and (7) 2-min step test (aerobic endurance). Anxiety will be assessed using the Generalized Anxiety Disorder Scale (GAD-7) (Dear et al., 2011), while depressive symptoms will be assessed using the Patient Health Questionnaire-9 (PHQ-9) (Löwe et al., 2004). Sleep quality will be determined by the Pittsburgh Sleep Quality Index (PSQI) (Buysse et al., 1989), and health-related quality of life will be measured using the validated Chinese version of the Short Form Health Survey questionnaire (SF-12) (Ware et al., 1996). All these assessment tools have been demonstrated to have relatively good reliability and validity when used with the Chinese population.

###### Other collected data

3.2.6.1.5

Adherence to the program will be documented via an activity diary completed by the research assistants, and reasons for dropouts and poor adherence will also be documented. Reasons for dropout, including adverse events, medical problems, death, and participant decisions, will be collected. Program satisfaction will be evaluated using a self-designed questionnaire. Participants will rate their satisfaction based on perceived enjoyment of the training, the appropriateness of the content, the form of the training, the benefits obtained by the training, and the likelihood of recommending the program to others. Rating will use a 4-point Likert scale, with “1” indicating “not at all” and “4” representing “definitely.” Any adverse event, such as muscular soreness, falls, or injury, will also be recorded by the research team.

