#### Study design, setting, and participants

3.2.1

This mixed methods study comprises a single-blind (outcomes assessor) randomized controlled trial (RCT) and a descriptive qualitative study. It will be conducted in community settings targeting older adults with cognitive frailty in Changsha City, Hunan Provence, China. Community settings will be chosen based on approval from local committees and the availability of eligible older adults. To engage older residents and encourage their participation, we will utilize posters, flyers, and social media platforms to disseminate information about the study. Additionally, recruitment will be conducted in collaboration with healthcare personnel who are responsible for the preventive home visits for the local residents.

Inclusion criteria:

(1) Aged ≥60 years.(2) Fulfilling the definition of cognitive frailty, which includes:(a) pre-physical frailty or physical frailty (Fried frailty phenotype score ≥ 1), and.(b) Montreal Cognitive Assessment (MoCA) scored between 18 and 25, but in the absence of dementia (Kelaiditi et al., 2013).(3) Providing informed consent and voluntary participation in the study.

Exclusion criteria:

(1) Poorly controlled or severe status of cardiovascular diseases, chronic obstructive pulmonary disease, diabetes, or hypertension.(2) Inability to walk independently.(3) Severe hearing or visual impairments.(4) Other health conditions that prevent participation in sports exercise.(5) Currently enrollment in other intervention programs.

The trial will run for a 12-week period. Participants will be enrolled based on inclusion and exclusion criteria. Measurements will be conducted at baseline and at the end of the intervention period. An overview of the study design is presented in Figure 2. Regarding the qualitative study, a subgroup of participants assigned to receive the multicomponent exercise intervention will undergo semi-structured interviews to explore their perception of the program.

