#### Intervention

3.2.2

Based on literature review, interviews with cognitive frail older adults, and consultations with physiotherapist, a preliminary multicomponent exercise intervention has been recommended for older adults with cognitive frailty. During the 12-week multicomponent exercise intervention period, participants will engage in moderate physical exercise tailored to their individual abilities, with each session lasting 50 min, held 3 times per week in a group setting at the local community center. Trained research assistants will provide assistance during these sessions. To control for concomitant exercise and diet, all participants will be advised not to seek any other exercise and instructed to maintain their normal diets throughout their enrollment in the study.

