Aerobic exercise	Exergaming-based Ping-Pong aerobic exercise involves dynamic body movements, including swinging motions with virtual Ping-Pong paddles, upper body rotation to hit the ball accurately, and leg movements to position oneself correctly (about 20 min)
Resistance exercise	The action includes elastic-band pull-apart, front and lateral raises, elbow flexion/bicep curl, and elastic-band lateral leg abductions, etc. (about 20 min)
Cool-down	Freehand stretching and relaxing exercises involve the main muscles and joints of the whole body (about 5 min)

In the control group, participants will maintain their normal daily activities without receiving any special intervention. Throughout the 12-week intervention period, if participants engage in additional physical activity, they will be required to document the details, including the activity time, type, and intensity. To avoid cross-contamination between the two groups, control over the exergaming power switch will remain with the intervention team, not the participants. Additionally, the elastic bands provided during sessions will be collected afterwards rather than kept by the participants.

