#### Safety protocol

3.2.7

Several measures will be implemented to ensure participants’ safety during the intervention. (1) Participants meeting exercise contraindications or assessed as high risk for exercise-related injuries will be excluded. (2) Instructions for the exercise intervention will include healthy advice to prevent injuries. (3) Prior to each exercise session, the exercise supervisor will conduct a brief medical safety check following ACSM recommendations. (4) If the participant reports concerning health changes, alterations in medications/dosage, or exhibits abnormal vital signs (e.g., blood pressure ≥ 180/100 mmHg), their participation in activities will be immediately paused, until they are seen and cleared to proceed by the study physician. (5) Participants will periodically report their perceived effort level on the Borg Rating of Perceived Exertion scale during each session to ensure proper exercise intensity. (6) There will be a warm-up routine before each session, and a cool-down routine after completion. (7) A multidisciplinary team (e.g., nurses, geriatricians, physiotherapists) has been involved in designing and implementing this trial to eliminate possible risks and prioritize participants safety.

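### Adverse events have far more chances of being noticed in the exercise arm than among controls, and no common way of asking both arms is described

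*Protocol article*

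**What the plan says.** All places are in the protocol article.

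- **Recording of events (3.2.6.1.5, Other collected data):** "Any adverse event, such as muscular soreness, falls, or injury, will also be recorded by the research team". No question, interval or arm is specified.
- **Exercise arm (3.2.2, Intervention):** sessions are "held 3 times per week in a group setting at the local community center" during the 12-week period, and "Trained research assistants will provide assistance during these sessions". Section 3.2.7 (Safety protocol) adds: "Prior to each exercise session, the exercise supervisor will conduct a brief medical safety check".
- **Control arm (3.2.2):** "participants will maintain their normal daily activities without receiving any special intervention".
- **Schedule (3.2.1):** "The trial will run for a 12-week period" and "Measurements will be conducted at baseline and at the end of the intervention period".
- **Analysis (3.2.10, Data analysis):** "adverse events will be tabulated and summarized using descriptive statistics". The section does not say whether the table is split by arm.

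**The concern.** A fall without injury, a strain or a sore shoulder enters the data only if someone hears of it. Staff see exercise participants every two or three days and check their fitness to exercise each time. Controls, as far as the article describes, are next seen at week 12. By then a minor event may be weeks old, and participants were selected for MoCA scores of 18 to 25. The same event is therefore more likely to be counted in one arm than in the other.

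Describing the counts instead of testing them does not help, because the distortion lies in the counts. At stake is whether a by-arm table of falls and injuries can be taken at face value in a prefrail or frail population. A reader may see an excess in the exercise arm that is not there, or may put a real excess down to closer observation.

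**Working it through.** **1. Opportunities for an event to be noticed**

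| | Exercise arm | Control arm |
|---|---|---|
| Sessions with staff present (3.2.2) | 12 weeks x 3 = 36, at full attendance | none |
| Safety checks (3.2.7) | one per session, so up to 36 | none |
| Scheduled assessments after baseline (3.2.1) | 1 | 1 |
| Other between-visit elements | consultations and a WeChat group (3.2.3, Table 2) | a record of any extra physical activity, covering time, type and intensity (3.2.2) |

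The activity record is called for only when extra activity takes place, and it is not described as asking about falls, injuries or symptoms. The article prints no session total or adverse-event rate, so there is no stated figure to reproduce.

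**2. What unequal capture does to a by-arm table**

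Let p be the true 12-week risk, the same in both arms, and let c be the share of affected participants whose event is recorded.

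- Recorded risk = p x c
- Recorded risk ratio = (p x c_exercise) / (p x c_control) = c_exercise / c_control. The true risk cancels.
- False risk difference = p x (c_exercise - c_control)

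The arm size of 41 is from 3.2.4. **Neither p nor c is given in the documents; all values below are assumptions.** With p = 20% and c_exercise = 95%, the exercise arm shows 0.20 x 0.95 = 19%, or 7.8 of 41.

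| Assumed control capture | Control arm shows | Risk ratio | False difference |
|---|---|---|---|
| 80% | 16% (6.6 of 41) | 0.95/0.80 = 1.19 | 3 points |
| 50% | 10% (4.1 of 41) | 0.95/0.50 = 1.90 | 9 points |
| 30% | 6% (2.5 of 41) | 0.95/0.30 = 3.17 | 13 points |

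The difference scales with p. At p = 10% it is 1.5, 4.5 or 6.5 points; at p = 30% it is 4.5, 13.5 or 19.5 points. With equal capture, the expected ratio is 1.00 when true risks are equal.

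**3. Comparison with chance variation**

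At p = 20% and 41 per arm, the standard error of a difference is sqrt(2 x 0.20 x 0.80 / 41) = 0.088, or about 9 points. The illustrated bias runs from about a third of that to about one and a half times it.

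**The case against.** Several objections have force.

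- **The table may not be by arm.** Section 3.2.10 lists adverse events beside programme adherence and satisfaction, which concern the exercise programme, and the first example of an event is muscular soreness. A tolerability summary of the exercise arm alone is a natural reading, and it would carry no false excess. This stands. A reader might infer that the planned table will be biased, but the text supports that only for a by-arm reading. An exercise-only table would in turn say nothing about excess harm.
- **The lack of control contact is inferred.** The two time points in 3.2.1 concern measurements, and 3.2.6.1 does not tie adverse-event collection to those visits. A fuller protocol could include contacts with controls. A reader might conclude that controls have no contact before week 12, or that they are asked about events only then; the article states neither. What does stand in the text is the imbalance between staffed, checked sessions in one arm and a two-point schedule with no intervention in the other.
- **A harms comparison is not an objective.** The objectives and hypotheses name none, and the sample is sized on the frailty score. Even with equal capture, 41 per arm gives an imprecise comparison. A reader might infer that the trial fails in a stated aim; it does not. This limits the severity, but poor precision is no reason to add a systematic error.
- **36 is a ceiling.** It assumes full attendance. The safety check is a clearance to exercise, not a described adverse-event query. Both points are right, but the imbalance remains at lower attendance.

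**Conclusion.** The point holds as a minor one. As described, opportunities to notice an event differ sharply between the arms (up to 36 supervised sessions plus the week-12 visit, against the week-12 visit alone), and no common elicitation is given. If the adverse-event table is read by arm, the likely direction is over-counting in the exercise arm relative to controls, for events that depend on being reported. Deaths and events leading to dropout are less exposed, because reasons for dropout are collected with no restriction to one arm.

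The size cannot be derived from the document. The 3 to 13 points at an assumed 20% risk only show how assumed capture rates carry through to the table. The conclusion rests on two conditions: that the table is read by arm, and that no undescribed contact with controls evens out the ascertainment. The primary outcomes and the sample size are not affected.

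**What to change.** In 3.2.6.1.5, add one short checklist (falls, injuries, soreness, unplanned medical contact), with the same wording and the same recall period, for both arms at the existing week-12 visit. To protect the assessor blinding in 3.2.5, ask it after all outcome measurements are complete, or use a self-completed form, since answers about soreness or sessions could reveal allocation. In 3.2.10, base any between-arm summary on that checklist alone, and report events observed at sessions in a separate table for the exercise arm only.

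The cost is a few minutes per participant and one extra table, with no new visit. There are two drawbacks. Recall over 12 weeks in people with cognitive impairment will miss events, though the under-counting should be similar in both arms. Participants who leave before week 12 will not complete the checklist; for them the recorded reasons for dropout remain the source.
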